## 8. SUMMARISED PATIENT PATHWAYS

[figure not shown]

a Scheduled to receive 45 Gy-55Gy long course radiotherapy (inclusion criterion 4). b Treatment decision should be made prior to registration (planned choice is a randomisation stratification variable). Medical oncologist may choose to use CAPOX or FOLFOX, or single agent capecitabine or 5-FU if concomitant use of oxaliplatin is contraindicated. c If patient defers surgery then the remaining 12 weeks of chemotherapy should be given as soon as possible following the repeat MRI scan and MDT meeting.

The trial design gives rise to three possible pathways: Control Arm; Intervention Arm Good Response to CRT and Intervention Arm Poor Response to CRT. Investigators should ensure the patient pathways described in this protocol are followed. However, if an individual patient deviates from the planned pathway through their choice, e.g. patient in the 'good response' subgroup of the Intervention arm opts for surgery, then this should be recorded on the **PROTOCOL DEVIATION Form**.

All patients should follow the registration and randomisation procedure described in Section 7 of the protocol. Following Randomisation the PI at each site will be informed of which arm the patient has been randomised to and the appropriate patient pathway described below should be followed:

## **8.1 THE CONTROL ARM – BEST CURRENT PRACTICE**

1. **Post-CRT restaging** – The post-CRT MRI must be **performed within 4-6 weeks (no later than 10 weeks)** from completion of CRT.
2. The radiologist will be notified that the patient has been randomised into the control arm. Radiologist completes the **CONTROL ARM POST-TREATMENT MRI Form**.
3. **Surgery** is planned according to the baseline MRI and should be performed 6-12 weeks after CRT completion. A prepared **SURGERY Form** should be enclosed in the patient notes so that the surgeon can complete the form immediately after surgery.
4. A routine surgical follow up appointment will occur 4-6 weeks after surgery, therefore the **SURGICAL MORBIDITY** and **PATHOLOGY REPORTING Forms** should be completed at 6 weeks. These forms may be completed retrospectively up to 12 weeks after surgery but only complications that occur within the first 6 weeks should be recorded on the **SURGICAL MORBIDITY Form**.
5. **Adjuvant Chemotherapy** - Please complete the **CHEMOTHERAPY and TOXICITY Forms** at the end of each cycle i.e. at the end of each 3-weekly cycle of CAPOX (or single agent capecitabine) or at the end of each 2-weekly cycle of FOLFOX (or single agent 5-FU).
6. **Oncological outcomes** – 12 months from the completion of CRT please complete the **ANNUAL FOLLOW-UP Form**, and further **SURGICAL MORBIDITY** and **TOXICITY Forms** to capture late surgical complications and residual toxicity respectively. To avoid the inevitable distress caused by the relative of a dead patient receiving questionnaires, please ensure this is completed in parallel with the follow-up for Patient Reported Outcome Measures (PROMs).
7. **PROMs** – 12 months from the completion of CRT, the recruiting trial site will need to invite the patient to complete a postal questionnaire (**QUALITY OF LIFE forms**) that includes 40 questions about symptoms and quality of life. The patient will have completed the questionnaires at entry into the study and will be expecting to receive the forms. A freepost envelope addressed to the recruiting trial site will also be provided. If the patient does not initially respond please contact them by phone – to

confirm the questionnaires arrived and to re-send if necessary. If there is no response send a second questionnaire 2 weeks later. If there is no response by 12 weeks (15 months from the end of CRT), we will accept that the patient preferred not to take part. If the patient has a disability that prohibits them from completing the forms by hand we recommend reading the questions out over the phone.

8. **Oncological outcomes** – 24 months and 36 months from the completion of CRT please complete the **ANNUAL FOLLOW-UP Form**.
9. **PROMs** - 36 months (not at 24 months) from the completion of CRT the patients will be asked to completed the same **QUALITY OF LIFE Form**.

## **8.2 INTERVENTION ARM – A ‘GOOD RESPONSE’ TO CHEMORADIOOTHERAPY (MRTRG 1 & 2)**

1. **Post-CRT restaging** – The post-CRT MRI must be **performed within 4-6 (no later than 10) weeks** of completing CRT. Ensure the Radiologist receives the appropriate reporting form – **INTERVENTION ARM POST-TREATMENT MRI Form** which includes the mrTRG datafields.
2. Radiologist completes the INTERVENTION ARM POST-TREATMENT MRI Form – **mrTRG 1 or 2 reported mrTRG directed management results in the patient being offered deferral of surgery.**
3. The option of deferral of surgery is discussed with the patient, and intensive active monitoring is undertaken. **Please refer to the 5 year surveillance schedule in Section 11.2 Deferral of Surgery Follow-up.** The **INTERVENTION ARM POST-TREATMENT MRI Form** should be completed each time an MRI scan is performed during the surveillance period.
4. **Chemotherapy** (Appendix 2) – The patient will receive 24 weeks of chemotherapy (8 cycles of CAPOX or 12 cycles of FOLFOX) and this should start within 12 weeks of CRT completion. Please complete the **CHEMOTHERAPY AND TOXICITY Forms** at the end of each cycle i.e. at the end of each 3-weekly cycle of CAPOX (or single agent capecitabine) or at the end of each 2-weekly cycle of FOLFOX (or single agent 5-FU).
5. **Mid-chemotherapy MRI scan** – an MRI scan should be performed approximately mid-way through chemotherapy treatment once the patient has received 12 weeks of treatment. The **INTERVENTION ARM POST-TREATMENT MRI Form** should be completed.
6. **Oncological outcomes**– 12 months from the completion of CRT please complete the **ANNUAL FOLLOW-UP Form**, and a further **TOXICITY Form** to assess residual toxicity. To avoid the inevitable distress caused by the relative of a dead patient receiving questionnaires, please ensure this is completed in parallel with the follow-up for Patient Reported Outcome Measures (PROMs).
7. **PROMs** -12 months from the end of CRT, the recruiting trial site will need to invite the patient to complete a postal questionnaire (**QUALITY OF LIFE Form**) that includes 40 questions about symptoms and quality of life. The patient will have completed the questionnaire at entry into the study and will

be expecting to receive the forms. A freepost envelope addressed to the recruiting trial site will also be provided. If the patient does not initially respond please contact them by phone – to confirm the questionnaires arrived and to re-send if necessary. If there is no response send a second questionnaire at 2 weeks later. If there is no response by 12 weeks (15 months from the completion of CRT), we will accept that the patient preferred not to take part. If the patient has a disability that prohibits them from completing the forms by hand we recommend reading the questions out over the phone.

8. **Oncological outcomes** – 24, 36, 48 and 60 months following the completion of CRT please complete the **ANNUAL FOLLOW-UP Form**.
9. **PROMs** - 36 months (not at 24 months) and 60 months from the completion of CRT the patients will be asked to complete the same postal questionnaire (**QUALITY OF LIFE Form**).

### **8.2.1 PROCEDURE IF A PATIENT DECLINES DEFERRAL OF SURGERY**

Complete a **PROTOCOL DEVIATION Form**. Follow-up and completion of CRFs should be carried out according to the control arm (Section 10.1, Assessment Schedule Control Arm and Section 11.1, Post-Surgery Follow Up). The patient is still eligible for analysis on an intention to treat basis.

### **8.2.2 PROCEDURE IF A LOCAL REGROWTH IS DETECTED**

Patients with evidence of clinical or radiological local regrowth or pelvic relapse must be treated at least as urgently as a primary rectal cancer by the surgical team. Refer to suspected regrowth pathway in Section 8.2.3 below. Complete a **SURVEILLANCE CRF**. If patient proceeds to surgery Follow-up and CRF completion should be carried out according to the Control arm (Section 10.1, Assessment Schedule Control Arm and Section 11.1, Post-Surgery Follow Up). The **SURGERY, SURGICAL MORBIDITY** and **PATHOLOGY REPORTING Forms** should be completed when the patient undergoes surgery. If the colorectal MDT decision is to offer adjuvant therapy then the **CHEMOTHERAPY** and **TOXICITY Forms** should also be completed during treatment. The timing of the oncological outcomes, assessment of late surgical complications and PROMs should be completed as per protocol.

If patient refuses surgery or is not fit for surgery then a **DISCONTINUATION OF TRIAL TREATMENT Form** should be completed and the patient followed-up unless they withdraw consent to further data collection.

The patient is still eligible for analysis on an intention to treat basis.

### 8.2.3 SUSPECTED REGROWTH PATHWAY FOR PATIENTS WHO DEFER SURGERY

[figure not shown]

### 8.3 EXPERIMENTAL ARM – A ‘POOR RESPONSE’ TO CHEMORADIOOTHERAPY

1. **Post-CRT restaging** – The post-CRT MRI must be performed within 4-6 (no later than 10) weeks of completing CRT.
2. Radiologist completes the **INTERVENTION ARM POST-TREATMENT MRI Form – mrTRG 3 –5 reported.**
3. **mrTRG directed management results in the patient being offered additional chemotherapy before a decision is made regarding surgery.**
4. The option of **additional pre-operative chemotherapy** is discussed with the patient. **Chemotherapy** (Appendix 2) – The patient will receive 12 weeks (4 cycles of CAPOX or 6 cycles of FOLFOX); this should start within 12 weeks of CRT completion. Please complete the **CHEMOTHERAPY** and **TOXICITY Forms** at the end of each cycle i.e. at the end of each 3-weekly cycle of CAPOX (or single agent capecitabine) or at the end of each 2-weekly cycle of FOLFOX (or single agent 5-FU).
5. Following the completion of 12 weeks of chemotherapy a repeat MRI should be performed 4-6 weeks later and mrTRG reported. Ensure the Radiologist receives the appropriate reporting form – **INTERVENTION ARM POST-TREATMENT MRI Form** which includes the mrTRG data fields. The Radiologist completes the **INTERVENTION ARM POST-TREATMENT MRI Form**.

**mrTRG directed management results in the patient being offered deferral of surgery (if mrTRG improved to I or II) or proceeding to surgery (mrTRG remains III-V). The options of surgery or deferral of surgery as appropriate should be discussed with the patient.**

- If mrTRG now I or II and it is agreed that patient should defer surgery then patients should receive the remaining 12 weeks of chemotherapy as soon as possible following the repeat MRI and MDT meeting and be followed up in the same way as those in the ‘good-response’ sub-group described above and undergo the 5 year surveillance schedule detailed in Section 11.2.1.

- If mrTRG remains III-V then patient proceeds to surgery and undergoes the following:

6. **Surgery** is planned according to the baseline and post-treatment MRI and should be performed **6-12 weeks after pre-operative chemotherapy** is completed. A prepared **SURGERY Form** should be enclosed in the patient notes so that the surgeon can complete the form immediately after surgery.
7. A routine surgical follow up appointment will occur 4-6 weeks after surgery, therefore the **SURGICAL MORBIDITY** and **PATHOLOGY REPORTING Forms** will be completed at 6 weeks. The **SURGICAL MORBIDITY Form** may be completed retrospectively up to 12 weeks after surgery but only complications that occur within the first 6 weeks should be recorded.

8. **Adjuvant Chemotherapy** - The patient will receive 12 weeks (4 cycles of CAPOX or 6 cycles of FOLFOX). Please complete the **CHEMOTHERAPY** and **TOXICITY Forms** at the end of each cycle i.e. at the end of each 3-weekly cycle of CAPOX (or single agent capecitabine) or at the end of each 2-weekly cycle of FOLFOX (or single agent 5-FU).
9. Oncological outcomes – 12 months from the end of CRT please complete the ANNUAL FOLLOW-UP Form, and a further **SURGICAL MORBIDITY** and **TOXICITY Forms** to capture late surgical complications and residual toxicity respectively. To avoid the inevitable distress caused by the relative of a dead patient receiving questionnaires, please ensure this is completed in parallel with the follow-up for Patient Reported Outcome Measures (PROMs).
10. **PROMs** -12 months from the end of CRT, the recruiting trial site will need to invite the patient to complete a postal questionnaire (**QUALITY OF LIFE Form**) that includes 40 questions about symptoms and quality of life. The patient will have completed the questionnaire at entry into the study and will be expecting to receive the forms. A freepost envelope addressed to the recruiting trial site will also be provided. If the patient does not initially respond please contact them by phone – to confirm the questionnaires arrived and to re-send if necessary. If there is no response send a second questionnaire at 2 weeks later. If there is no response by 12 weeks (15 months from the end of CRT), we will accept that the patient preferred not to take part. If the patient has a disability that prohibits them from completing the forms by hand we recommend reading the questions out over the phone.
11. **Oncological outcomes** – 24 months and 36 months following the end of CRT please complete the **ANNUAL FOLLOW-UP Form**.
12. **PROMs** - 36 months (not at 24 months) following the end of CRT the patients will be asked to complete the same **QUALITY OF LIFE form**.

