#### 4.4.2 SECONDARY ENDPOINTS

- The pCRM rate will be compared between the control and investigation arms.
- The strength of agreement of the reported mrTRG will be evaluated between the site radiologist versus the central radiologist at site initiation and at the end of the feasibility trial.
- Acute toxicity will be recorded to CTCAE v4.0 protocol. The grade 3- 5 adverse events will be compared between the control and intervention arms on an intention to treat basis.
- Early (30 day) and late (up to 12 months) surgical morbidity will be reported according to the Clavien-Dindo classification
- Quality of surgery will be determined by using the mesorectal grading system and a similar system will be used for grading the quality of APE specimens (Pathology appendix). Outcomes will be compared between the control and intervention arms on an intention to treat basis.

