### 14.2.2 SECONDARY ENDPOINTS

All secondary endpoints will be summarised using descriptive statistics, and will be used to inform the design of the proposed phase III study. The following limited number of endpoints will be summarised by arm, and within arm by patients grouped by mrTRG 1-2 vs. 3-5. Exploratory comparison between arms will be carried out using Fisher's exact test for categorical variables (pCRM rate, proportion with unsalvageable regrowth, proportion of patients with any one or more grade 3-5 toxicity). Quality of surgery and surgical morbidity (maximum Clavien-Dindo grade per patient) will be compared between arms using a Mann-Whitney test. No other formal statistical comparison will be made between arms or mrTRG subgroups for endpoints not listed below.

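### The late surgical morbidity form is timed from the end of CRT, not from surgery, so operated poor responders have about half the post-operative observation of control patients

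*Protocol*

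**What the plan says.** Section 4.4.2 of the Protocol sets the endpoint: "Early (30 day) and late (up to 12 months) surgical morbidity will be reported according to the Clavien-Dindo classification". It does not say from what date the 12 months run, and section 14.2.2 repeats the wording. The introduction to section 10 says early and late complications are recorded post-operatively, again without an origin.

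The pathway text supplies the clock.

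- **Control, section 8.1 point 6:** "12 months from the completion of CRT please complete the" ANNUAL FOLLOW-UP Form, together with a further SURGICAL MORBIDITY Form for late complications.
- **Poor responders, section 8.3 point 9:** "12 months from the end of CRT please complete the ANNUAL FOLLOW-UP Form, and a further" SURGICAL MORBIDITY Form.
- **Tables 10.1 and 10.3:** the second surgical morbidity entry sits in the 12-month column, which counts months from the end of CRT. The later annual visits have no such entry.

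Surgery is timed differently in the two pathways. In control it "is planned according to the baseline MRI and should be performed 6-12 weeks after CRT completion" (section 8.1 point 3). In poor responders pre-operative chemotherapy comes first: "this should start within 12 weeks of CRT completion". It lasts 12 weeks, and surgery follows 6-12 weeks after it ends (section 8.3 points 4 and 6).

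For surgery after regrowth, section 8.2.2 asks for the surgery, morbidity and pathology forms at the operation and then says: "The timing of the oncological outcomes, assessment of late surgical complications and PROMs should be completed as per protocol".

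On analysis, section 14.2.2 says that "surgical morbidity (maximum Clavien-Dindo grade per patient) will be compared between arms using a Mann-Whitney test".

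The early form is tied to the operation. Section 8.1 point 4 says "only complications that occur within the first 6 weeks should be recorded on the" SURGICAL MORBIDITY Form, and section 8.3 point 7 sets the same limit.

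**The concern.** A maximum grade can only stay the same or rise as observation lengthens. If one arm is operated on months later but both arms are closed out on the same CRT-based date, the later-operated patients have less time in which a late complication can be recorded. The strategy under test would then look somewhat gentler for a reason unrelated to treatment.

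This matters because section 3.1 names safety as a purpose of the feasibility study and says its patients will enter the final phase III analysis. A late complication that no scheduled form collects cannot be recovered later by an analysis plan.

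**Working it through.** The protocol states no figure for this point, so the check is timeline arithmetic from its own windows, with 12 months taken as 52 weeks.

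**Formula.** Post-operative weeks covered by the late form = 52 − (week of surgery, counted from the end of CRT).

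**Control.** Surgery at weeks 6-12 gives 52 − 12 = 40 to 52 − 6 = 46 weeks (midpoint 43).

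**Poor responders who have surgery.** The protocol gives only a latest start for chemotherapy, week 12. The earliest start is an assumption: not before the post-CRT MRI, so about week 4.

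- Week of surgery: 4 + 12 + 6 = 22 at the earliest, 12 + 12 + 12 = 36 at the latest.
- Weeks covered: 52 − 36 = 16 to 52 − 22 = 30 (midpoint 23).

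**Ratio of poor responders to control.** Midpoints 23/43 = 0.53; extremes 16/46 = 0.35 and 30/40 = 0.75. The two ranges do not overlap.

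**Sensitivity to the assumed start.**

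| Chemotherapy start (weeks after CRT) | Weeks covered, poor responders | Midpoint ratio to control |
|---|---|---|
| 4-12 | 16-30 | 0.53 |
| 6-12 | 16-28 | 0.51 |
| 12 only | 16-22 | 0.44 |

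**Late period only** (after the 6 weeks of the early form, start 4-12): control 34-40 weeks, poor responders 10-24 weeks, midpoint ratio 17/37 = 0.46.

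**Surgery for regrowth.** Surveillance after deferral runs for 5 years (section 11.2.1). If the operation comes after week 52, the month-12 form has already passed. The early form still applies; no late form is scheduled.

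**Does the adverse event form fill the gap?** It also takes surgical events (Appendix 1, section 2), but recording stops 30 days (4.3 weeks) after the last chemotherapy dose. Assume adjuvant treatment starts 4-12 weeks after surgery (Appendix 2, section 1.1) and is completed without delay.

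- Control, 24 weeks of treatment: 4 + 24 + 4.3 to 12 + 24 + 4.3, about 32-40 post-operative weeks.
- Poor responders, 12 weeks of treatment: 4 + 12 + 4.3 to 12 + 12 + 4.3, about 20-28 weeks.

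The imbalance runs the same way.

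**Illustration only.** The protocol gives no late complication rate. Assume the same constant late hazard in both arms and a true risk of 20% between post-operative weeks 6 and 52. Then h = −ln(0.80)/46 = 0.00485 per week, and the observed risk is 1 − exp(−h × late weeks).

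- Control, 37 late weeks: 16.4%.
- Poor responders, 17 late weeks: 7.9%.

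A true risk of 10% would appear as 8.1% versus 3.8%, and 30% as 24.9% versus 12.3%.

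**Early window, side by side.** It is 30 days in sections 4.2 (objective 3), 4.4.2 and 14.2.2. It is 6 weeks in sections 8.1, 8.3 and the introduction to 10, and 4-6 weeks in the footnotes to tables 10.1 and 10.3.

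**The case against.** Several stronger readings are tempting, and the documents do not support them.

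- **The whole intervention arm is under-observed.** It is not. The shortfall concerns poor responders who reach surgery and patients operated for regrowth. Good responders who decline deferral follow the control schedule (section 8.2.1). Patients never operated on have no post-operative window, and section 8.2 itself asks for no late morbidity form.
- **Morbidity of surgery after regrowth is lost altogether.** Section 8.2.2 requires the morbidity form at the operation, so early capture remains; only late capture is missing. Appendix 4 stresses surgical morbidity in general for these patients and does not single out late complications.
- **The comparison is shown to favour the intervention.** The shorter window pushes that way, all else equal, but the net direction is not established. Operated intervention patients are mainly poor responders who have had extra chemotherapy, whereas control operates on all response grades, and this may push the other way. Section 14.2.2 also does not say whether the maximum pools early and late complications. An early-only maximum has equal exposure in both arms.
- **Patients without surgery should be scored grade 0.** That would itself favour the arm that defers surgery, and it is not proposed here.

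It is also fair to say that the primary endpoint is recruitment, that this comparison is exploratory, that 90 patients are planned, and that secondary objective 3 names only 30-day morbidity, reported descriptively. The 30-day versus 6-week difference applies equally to both arms and adds nothing to the exposure imbalance.

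What stands is that late morbidity is a listed endpoint, its collection date is fixed in the protocol on the CRT clock, and no other form restores equal observation.

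**Conclusion.** The point holds within those limits. On the protocol's own schedule the late form covers 40-46 post-operative weeks in control and about 16-30 in operated poor responders, roughly half at the midpoints. The lower end of that ratio depends only on stated windows; the upper end depends on the assumed week-4 start. Regrowth surgery after month 12 has no scheduled late form.

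A between-arm comparison of late morbidity, or of a maximum grade that includes late events, therefore rests on unequal exposure that, all else equal, lowers the observed grade in the intervention arm. The resulting bias cannot be sized from the document. The early comparison and the recruitment endpoint are unaffected. The change should be made because it corrects data collection that is meant to carry into phase III.

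**What to change.** 1. In sections 8.1, 8.2.2 and 8.3 and tables 10.1 and 10.3, make the late SURGICAL MORBIDITY Form due 12 months after the date of surgery, including surgery for regrowth, and record the date of each complication. State the same origin in sections 4.4.2, 10 and 14.2.2. Every operated patient then has 52 scheduled post-operative weeks.
2. For data already collected on the CRT clock, compare arms only over a common post-operative window: the 6-week early form for all operated patients, or about 16 weeks for control and on-schedule poor responders where complications are dated.
3. Reconcile the early window across sections 4.2, 4.4.2, 8.1, 8.3, 10 and 14.2.2, either as 30 days taken from dated complications or as 6 weeks throughout.

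**Cost.** Form timing and wording only; no treatment timing changes. The form would fall at weeks 58-64 from CRT in control (6 + 52 to 12 + 52) and weeks 74-88 in poor responders (22 + 52 to 36 + 52), so after the month-12 visit, and later still for regrowth surgery. It can be completed from the notes at the next scheduled visit, a small added burden for sites.
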